## 1 Introduction

In 2019, an estimated 10 million people, out of 1.7 billion carriers of *Mycobacterium tuberculosis* (*Mtb*), fell ill with tuberculosis (TB) and 7.1 million patients received TB treatment. Adolescent males accounted for most TB cases in 2019 (56%). 8.2 % of all cases had a positive human immune-deficiency virus-1 (HIV) status. Globally, the highest incidence of TB can be found in South-East Asia (44%) followed by Africa (25%) and the Western Pacific (18%). [1] TB and HIV are two of the leading infectious causes of death worldwide and TB is the leading cause of death in people living with HIV (PLWH). [2, 3] There were approximately 37.9 million PLWH worldwide in 2018, of which almost two thirds (25.7 million) lived in Africa. In South Africa, the country having the largest HIV epidemic in the world, the prevalence of HIV in adolescence (15 to 49 years) was 19% in 2019, whereas the total incidence of TB was 615 per 100,000 in 2019, which leads to the highest burden of HIV co-infected cases globally. [1, 5, 6] The mortality in TB patients almost doubled with HIV co-infections from 22,000 cases (TB without HIV) to 36,000 cases (TB with HIV) in 2019. 7.1% of the previously treated TB cases and 3.4% of the new TB cases in 2019 were resistant to rifampicin and/or Isoniazid in South Africa. (1) PLWH are more likely to develop extrapulmonary TB (EPTB). [11, 12]

Approximately 10-20% of EPTB accounts for skeletal TB with spinal involvement in 50-60% of the cases. [15-17] It is believed that spinal involvement occurs from the spread of *Mtb* from a primary lesion, either pulmonary lesion or from a urogenital infection.

Spinal TB (spondylitis or spondylodiscitis caused by *Mtb*), also called Pott's disease, usually results in local pain, neurological deficit, spinal instability and fever and duration from initial symptoms to adequate diagnosis can take up to several years. [19-21] Diagnosis depends on clinical appearance, imaging, and microbiological confirmation from biopsies. [17] Treatment usually consists of primary chemotherapy, immobilization, and spinal surgery in selected patients. [22] Magnetic resonance imaging (MRI) has a reported specificity of 93% and a sensitivity of 94% in detecting spondylodiscitis and therefore is the current gold standard imaging modality of spinal TB. [23] Spinal cord compression, intrinsic changes of the cord, bony changes of the vertebral body as well as the extent of disc destruction can be detected with high accuracy. [24] If possible, MRI of the whole spine should be performed to detect non-continuous lesions, which occur in 15 to 20% of the patients. [25]

18F-fluorodeoxyglucose (18-FDG) positron emission tomography (PET)/computed tomography (CT) - PET/CT - has recently been shown to be able to detect sites of infection and monitor treatment success. 18-FDG accumulates in tissues with altered glucose metabolism (e.g., malignant conditions, ischemia, inflammatory conditions). It has been found that 18-FDG uptake values are higher in patients with spinal TB compared to patients with pyogenic spondylitis. [43] A recent study has shown that PET/CT is superior to MRI in terms of specificity in the diagnosis of spinal TB. [26] Host transcriptomics have identified a RNA signatures for diagnostics as well as understanding the immunological mechanisms of TB. [27] Several RNA signatures for capillary blood-based PCR-tests have been identified for risk of disease stratification, screening for TB, tracking treatment response and prediction of treatment failure. [28-31] Lately, an RNA signature which predicts recent exposure to *Mtb* in humans has been identified. [32] The description of these signatures are opening the possibility for developing large-scale point of care screening test as well as targeted (personalized) intervention to prevent the disease and, in patients with active tuberculosis, create customized treatment plans. [29]

## 2 Rationale

The purpose of this proposal is to describe the clinical phenotype of spinal TB using whole body PET/CT and to identify a mRNA gene expression profile of isolated spinal TB versus disseminated spinal TB stratified by HIV status.

*Mtb* infection of the spine is believed to be due to hematogenous dissemination from a primary focus into the well perfused cancellous bone of the vertebral bodies. [34, 35] With this, the question arises, if isolated TB spine without any other active focus can be a stand-alone entity and if the genome of mycobacterium tuberculosis differs between the different sites of disease. In up to 68% of HIV patients with spinal involvement, mycobacterium tuberculosis was identified as the source of spinal lesions and most of these patients had an advanced HIV-infection, which makes it necessary to stratify this cohort by HIV-status. [39, 40] PET/CT-Scan has recently been shown to be able to detect sites of active infection and monitor treatment response. Additionally, PET/CT may discriminate spinal infection from other spinal processes, and it has been shown that the SUVmax levels in tuberculous

spondylodiscitis are significantly higher compared to cases with pyogenic spondylitis. [42, 43]. In addition, SUVmax will direct to the site for biopsy. [41] Whole-genome sequencing allows for strain typing and identification of multiple strain infection. [44] Different strains have been identified as the cause for a different phenotypical pattern of disease. [45] In our Spinal TB X cohort, we aim to describe the clinical phenotype of spinal TB using whole body PET/CT and identify a specific gene expression profile for the different stages of dissemination and compare our findings to previously described signatures for latent and active pulmonary TB. Currently, the definite diagnosis of spinal tuberculosis is made either by open surgery or CT-guided biopsy to collect specimens for microbiological work up. A blood-based test for spinal TB would lead to earlier diagnosis and treatment in all settings globally and improve treatment outcome of this devastating disease.

### 3 Study Hypothesis and Objectives

#### Hypothesis

1. We hypothesize that spinal TB may present as two clinical phenotypes: isolated spinal TB with no additional lesion on whole body PET/CT and disseminated spinal TB with a spinal lesion plus an additional extraspinal lesion on whole body PET/CT.
2. We hypothesize that a specific gene expression profile may distinguish between the two clinical entities above and allows for treatment monitoring during antimicrobial therapy ("personalized medicine")
3. We hypothesize that whole body PET/CT is superior to MRI in diagnosing spinal and extraspinal TB.

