#### Secondary objectives

1. To identify the distributive patterns of suspected spinal TB using two imaging modalities: MRI and PET/CT.
2. To analyse the genomes of *Mtb.* extracted from different sites of the body (if available) and to identify differences in their genome regarding SNPs and drug sensibility.
3. To analyse scintigraphic findings using PET/CT at treatment initiation, 6 months, and 12 months to better understand treatment outcome using PET/CT.
4. To compare imaging findings on PET/CT and MRI at baseline to evaluate the role of PET/CT in spinal TB diagnostics (virtual biopsy).

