### 4 Study design, population, and eligibility

#### 4.1 Design

This is a prospective cohort study to develop new diagnostic biomarkers for isolated spinal TB versus disseminated spinal TB and treatment monitoring. Furthermore, this study investigates genetic variability of *Mtb.* in spinal TB and its distributional pattern. After MRI-confirmation of spinal TB according to local algorithms, patients will be invited to join the study. At baseline, clinical examination as well as blood biobanking will be performed. Every patient with unknown HIV status will undergo HIV-testing. Sputum will be collected for *Mtb.* culture and GeneXpert as well as specimens from other sites of TB diseases (e.g. urine, FNA) and screening for diabetes and pregnancy will be performed. Whole-body PET/CTs will be performed at time of diagnosis (0 month), 6 months, and 12 months of treatment. Either spinal biopsies or surgery will be performed according to clinical indication to confirm the diagnosis of spinal TB at baseline after imaging modalities have been performed (MRI and PET/CT).

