## 4.2 Participant characteristics

Participants with clinically and MR-suspected spinal TB will be recruited from Groote Schuur Hospital, Cape Town, South Africa, its affiliated hospitals, UCT Private Academic Hospital and other private hospitals in the region. According to the current caseload, we will be able to include 50 participants per year, aiming for 100 participants in total. However, if recruitment goals cannot be achieved according to aim, Tygerberg Hospital, Cape Town, South Africa may be approached to enhance recruitment. In result, we are aiming for 300 PET/CTs (100 initial, 100 at 6 months, 100 at 12 months) and 300 peripheral blood samples for gene expression analysis.

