## 4.3 Eligibility Criteria

### Inclusion Criteria

1. Participant has completed the written informed consent process prior to undergoing any clinical evaluations and willing to undergo HIV testing
2. TB spine based on clinical and radiological criteria
3. Age 18 or older with a body weight of at least 40 kg body weight
4. Able and willing to return to follow-up
5. Willing to have samples, including DNA including RNA extraction, stored
6. Willing to consistently practice a highly reliable method of pregnancy prevention

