#### 5.1 Participant Screening (SCR)

Participants with a confirmed diagnosis of spinal TB based on clinical presentation and MRI will be enrolled. participants who sign the **Main Informed Consent Form and HIV-Testing Consent Form** will undergo screening. The following will then be performed/obtained:

1. Vital Signs
2. Medical history and co-medications
3. Physical examination (including neurology)
4. Induced sputum samples (total sputum volume at least 3 mL) for TB culture (MGIT) and GeneXpert Ultra (Xpert).
5. Urine sample for TB culture (MGIT) and GeneXpert Ultra (Xpert)
6. Blood draw for (fasting prior to phlebotomy, max. 50 mL):
  1. Full blood count (including differential), serum chemistry (ALT, creatinine, hsCRP)

2. Diabetes screening (HbA1c)
3. HIV-1 ELISA testing, for all patients not on ART
4. CD4 count and HIV-1 viral load, for all participants tested positive for HIV or on ART
7. Finger prick for random glucose testing
8. Urine collection for pregnancy testing (beta-HCG)

Note that at this and all subsequent visits, if a sputum culture or blood sample is found to be contaminated or is otherwise unevaluable, the participant may be called back to provide another sputum sample. If for some reason a participant needs to come back the next day to provide sputum, this will not be a deviation. In addition, it will not be a protocol deviation if a participant is unable to provide sufficient sputa to perform all sputum-related testing at any study visit.

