## **6.13 Analysis**

Analysis will be performed using SPSS®. Continuous data will be analysed as median and interquartile range [IQR] and categorical data as frequencies (%) with their 95% confidence interval (CI) where appropriate. For comparing proportions between two groups, we use the chi-square (v2) test. Medians will be compared between two groups (HIV infected and HIV uninfected) using the Wilcoxon ranksum test. Univariate logistic regression will be performed and the cut-off P-value < 0.2 used for inclusion of variables in the multivariate logistic regression model. Multivariate logistic regression will use a stepwise backwards and manual intelligent techniques to identify the independent predictors of the composite endpoint of MS. The logistic regression models' results will be presented as odds ratios (OR) with the 95% CI. Statistical significance will be accepted at the two-sided level of  $P \leq 0.05$ . Sociodemographic and clinical data as well as laboratory findings will be analysed.

Semiquantitative PET/CT analysis will be performed using MIM® Software. Total lesion glycolysis (TLG) at the region of interest (ROI) will be measured as well as SUVmean, SUVmax and SUVvolume after subthreshold calculation of the ROI.

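### The spinal part of hypothesis 3 (PET/CT superior to MRI) cannot be shown in a cohort entered through a positive MRI, and the extraspinal part can only be described

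*Protocol*

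**What the plan says.** The third hypothesis, in the synopsis and in section 3, is "We hypothesize that whole body PET/CT is superior to MRI in diagnosing spinal and extraspinal TB". Secondary objective 4 serves it by comparing baseline findings on the two modalities, with the stated purpose "to evaluate the role of PET/CT in spinal TB diagnostics (virtual biopsy".

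Entry is described in four places:

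- Section 4.1: "After MRI-confirmation of spinal TB according to local algorithms, patients will be invited to join the study".
- Section 5.1: "Participants with a confirmed diagnosis of spinal TB based on clinical presentation and MRI will be enrolled".
- Section 4.2: "Participants with clinically and MR-suspected spinal TB will be recruited from Groote Schuur Hospital".
- Section 4.3, inclusion criterion 2: "TB spine based on clinical and radiological criteria", with no modality named.

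PET/CT follows this step. Spinal tissue comes from biopsy or surgery when clinically indicated (sections 4.1 and 5.4). Other sites of disease are sampled according to the PET/CT result and only if they can be reached conservatively (section 5.3). The imaging row of the schedule in section 5 lists PET/CT only, so the MRI is the one already done in routine care.

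**The concern.** A comparison of two diagnostic tests needs patients whom either test could have missed or wrongly labelled. Here one of the two tests decides who enters. For the spinal diagnosis at patient level, MRI has already been positive in everyone, so its errors of omission are out of sight and its false alarms are all retained.

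Two wrong conclusions could follow. PET/CT could look no better than MRI in sensitivity because the design does not allow it to be better. Or PET/CT could look better in specificity because MRI was given no chance to be negative. The second is the more likely to be published as a finding, since the Introduction already cites literature that PET/CT exceeds MRI on specificity and objective 4 carries the virtual-biopsy label. An analysis plan cannot repair this, because patients who were never enrolled cannot be recovered.

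**Working it through.** **1. The plan's own figure.** Section 4.2 expects 50 participants a year; over about 2 years, 50 × 2 = 100, and three scans each give 300 PET/CTs. Both figures reproduce. The 100 comes from caseload and is not tied to hypothesis 3.

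**2. The entry gate.** Sections 4.1 and 5.1 speak of MRI confirmation and section 4.2 of MRI suspicion. The strength of the MRI statement differs, but all three need an MRI that points to spinal TB. Criterion 2 in section 4.3 is silent on modality, and nothing elsewhere opens a route for MRI-negative patients. Exclusion criterion 5 also removes those whose MRI suggests malignancy.

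**3. Patient-level sensitivity, spinal TB.** Let T be the number enrolled with TB and t the number of them positive on PET/CT.

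- MRI: T / (T + 0) = 100%.
- PET/CT: t / T ≤ 100%.
- Difference, PET/CT minus MRI: t/T − 1 ≤ 0.

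A within-patient test rests on discordant patients, and the cell PET/CT-positive with MRI-negative is always 0. In 5,000 simulated cohorts of 100 MRI-positive patients (MRI sensitivity 94% and specificity 93% from the Introduction; TB prevalence before MRI assumed 70%), the mean difference was −10, −2 and 0 percentage points for assumed PET/CT sensitivities of 90%, 98% and 100%. It was never above 0, and PET/CT was superior in none.

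**4. Specificity, spinal TB.** Let N be the number enrolled without TB. MRI specificity is 0 / (0 + N): undefined if N = 0, and 0% if N > 0. With N > 0, PET/CT beats MRI as soon as it is negative in one such patient.

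The likely size of N, for assumed prevalence p among patients sent to MRI, follows from the cited MRI figures. They are quoted for spondylodiscitis, so applying them to spinal TB is a further assumption.

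- MRI-positive share: 0.94p + 0.07(1 − p)
- Non-TB per 100 enrolled: 100 × 0.07(1 − p) / share
- MRI-negative TB patients left out, per 100 enrolled: 100 × 0.06p / share

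| p (assumed) | Share | Non-TB per 100 enrolled | MRI-negative TB left out |
|---|---|---|---|
| 0.3 | 0.331 | 14.8 | 5.4 |
| 0.5 | 0.505 | 6.9 | 5.9 |
| 0.7 | 0.679 | 3.1 | 6.2 |
| 0.9 | 0.853 | 0.8 | 6.3 |

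The last column holds the only patients who could show PET/CT to be more sensitive.

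**5. Extraspinal TB.** Entry does not depend on MRI seeing anything outside the spine, so the two modalities can differ in either direction. Three features limit what the difference means:

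- Field of view: PET/CT runs from the skull base to the sub-trochanteric region (section 11.1). The MRI follows local algorithms with no field fixed. The Introduction says only "If possible, MRI of the whole spine should be performed to detect non-continuous lesions".
- Verification: section 5.3 samples sites that PET/CT points to. Sputum and urine are cultured in everyone at screening, so lung and urinary disease is partly checked independently, but PET/CT misses elsewhere are not sought.
- Spinal tissue depends on clinical indication, so that reference may also be incomplete.

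**6. What a real sensitivity test would need.** Suppose entry did not depend on MRI and all were verified. With MRI sensitivity 0.94, PET/CT sensitivity s, and independence of the two given TB, the discordant probabilities are b = 0.06s and c = 0.94(1 − s), with d = b − c. For two-sided 0.05 and assumed 80% power,

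n = [1.96√(b + c) + 0.842√(b + c − d²)]² / d².

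| s (assumed) | TB patients | Suspects at 70% prevalence |
|---|---|---|
| 0.98 | 379 | 542 |
| 0.99 | 214 | 306 |
| 1.00 | 129 | 185 |

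All exceed the planned 100.

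**The case against.** The best case for the protocol has four parts, and much of it stands.

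- *Specificity.* A reader might infer that no specificity can be estimated for either test. The documents do not support that. Section 4.2 recruits suspected cases, and tissue is taken after imaging to confirm the diagnosis, so some participants may prove not to have TB. PET/CT specificity among verified MRI-positive patients is then estimable, though on few patients. It is a legitimate virtual-biopsy question. What remains invalid is the contrast with MRI.
- *Extraspinal disease.* A reader might take the whole hypothesis to be blocked by the entry rule. It is not; only the patient-level spinal part is. Wider coverage is also a real advantage of a whole-body scan, but it should be reported as coverage and not as better diagnosis.
- *Lesions outside the MRI field.* From the Introduction's 15 to 20% with non-contiguous lesions, a reader might conclude that 15 to 20 of 100 patients will count as MRI misses. That is an upper bound, reached only if no MRI covers the whole spine; with whole-spine MRI the number outside the field is about zero.
- *The test.* Section 6.13 says "For comparing proportions between two groups, we use the chi-square" test, and a reader might object that the modalities are paired. But the protocol never assigns that test to PET/CT versus MRI, and the groups it goes on to name are HIV infected and uninfected. A paired method can be left to the analysis plan.

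Objectives 1 and 4 are worded as description or comparison of findings and can be met as they are. None of this rescues superiority for the spinal diagnosis.

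**Conclusion.** Hypothesis 3 is wrong as written for spinal TB. In this cohort MRI sensitivity is 100% and PET/CT cannot exceed it. This follows from the entry rule alone and needs no assumption about prevalence or PET/CT performance. MRI specificity is undefined or 0%, so no fair contrast exists there either. For extraspinal TB a comparison is possible, but as description only.

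The counts of about 1 to 15 non-TB participants and 5 to 6 omitted MRI-negative TB patients per 100 rest on the cited 94% and 93% and on an assumed prevalence of 30 to 90%. They indicate scale and the conclusion does not depend on them.

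The point deserves correction but is not critical to the study. The primary objective (phenotype on PET/CT and mRNA profiles) does not depend on hypothesis 3, and a reader should not conclude that the cohort as a whole is compromised.

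**What to change.** Reword hypothesis 3 in the synopsis and section 3 so that it no longer claims superiority over MRI in diagnosing spinal TB, and state what MRI-positive patients can answer:

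1. Additional vertebral levels or lesions on PET/CT versus MRI, counted only in the field that both scans cover and compared within patient. This requires the field of each MRI to be recorded.
2. The proportion with extraspinal lesions on PET/CT, descriptive only.
3. Among participants with a spinal culture or Xpert result, PET/CT findings such as SUVmax in confirmed TB versus not TB. Biopsy-negative participants stay in the dataset, and the result is stated to apply to MRI-positive, verified patients.

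Objective 4 can remain a comparison of findings, with the virtual-biopsy label confined to item 3. The wording on entry in sections 4.1, 4.2, 4.3 and 5.1 (confirmed, suspected, or radiological) should be reconciled, because it decides whether non-TB participants are expected.

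The cost is some rewording, one recorded variable and a more modest claim. Entry regardless of MRI with a reference standard in everyone would permit the original test, but at roughly 185 to 542 suspects under the assumptions above. It would also touch the indication for tissue sampling, which is a clinical matter, so it is not proposed here.

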#### Primary objective

To describe the clinical phenotype of spinal TB using whole body PET/CT and to identify and mRNA gene expression profiles of isolated spinal TB versus disseminated spinal TB stratified by HIV status.

#### Secondary objectives

1. To identify the distributive patterns of suspected spinal TB using two imaging modalities: MRI and PET/CT.
2. To analyse the genomes of *Mtb.* extracted from different sites of the body (if available) and to identify differences in their genome regarding SNPs and drug sensibility.
3. To analyse scintigraphic findings using PET/CT at treatment initiation, 6 months, and 12 months to better understand treatment outcome using PET/CT.
4. To compare imaging findings on PET/CT and MRI at baseline to evaluate the role of PET/CT in spinal TB diagnostics (virtual biopsy).

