### Exclusion Criteria

1. Pregnancy or active desire to become pregnant within the next 6 months.
2. Uncontrolled diabetes (HbA1c  $\geq 6.5\%$  / random glucose concentration  $\geq 11.1$  mmol/l, fasting plasma glucose  $\geq 7.0$  mmol/l)
3. Alcohol and substance abuse which might interfere with medication adherence during the trial
4. Positive SARS-CoV-2 PCR in the past 4 weeks
5. Suspicion of malignancy on MRI or known malignancy
6. Suspicion of inflammatory disease and other rheumatological conditions

7. Any person for whom the physician feels this study is not appropriate
8. Age under 18 years

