## **5.4 Surgery**

Surgery will be performed by the Department of Orthopaedics if indication is given. Should surgery be performed, spinal biopsies will be obtained for TB culture (MGIT) and GeneXpert Ultra (Xpert).

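### Secondary objective 4 judges PET/CT as a virtual biopsy against MRI alone; in an MRI-selected cohort that comparison leaves specificity largely unidentified, and the scheduled tissue results are not set against PET/CT

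*Protocol*

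**What the plan says.** The objective appears in the synopsis and again in Section 3, under Secondary objectives: "To compare imaging findings on PET/CT and MRI at baseline to evaluate the role of PET/CT in spinal TB diagnostics (virtual biopsy"). The bracketed term is not defined anywhere. Hypothesis 3 is related: "We hypothesize that whole body PET/CT is superior to MRI in diagnosing spinal and extraspinal TB". It names no reference standard either.

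On what settles the diagnosis, Section 2 (Rationale) says: "Currently, the definite diagnosis of spinal tuberculosis is made either by open surgery or CT-guided biopsy to collect specimens for microbiological work up". Section 4.1 uses tissue for that purpose: "Either spinal biopsies or surgery will be performed according to clinical indication to confirm the diagnosis of spinal TB at baseline", after both imaging methods. Section 5.4 adds: "Should surgery be performed, spinal biopsies will be obtained for TB culture (MGIT) and GeneXpert Ultra (Xpert"), and the schedule in Section 5 lists the same two tests under surgery or CT-guided biopsy.

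On entry, Section 4.1 invites patients after MRI confirmation, Section 4.2 speaks of clinical and MR suspicion, and Section 5.1 requires a diagnosis based on presentation and MRI.

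Section 6.13 (Analysis) lists descriptive statistics, chi-square and rank-sum tests, logistic regression and the PET uptake measures. It gives no accuracy measure and no reference standard.

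**The concern.** A biopsy supplies a microbiological result. If an image is to be called a virtual form of it, the natural question is how well the image predicts that result. Objective 4 asks how the image compares with another image, and MRI is also how participants were selected. A secondary analysis that followed the objective faithfully could report high concordance and still leave its diagnostic label unsupported. The tissue results that bear on the question would meanwhile sit in the database without a stated use for evaluating PET/CT.

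This is not a detail that a protocol normally leaves to its analysis plan. The objective itself fixes the comparator.

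**Working it through.** The protocol gives no sample size, power or accuracy figure for this objective. The target of 100 comes from caseload (50 per year, Section 4.2). There is therefore no figure of the plan to reproduce. Three checks follow.

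**1. What PET-MRI agreement identifies.**

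From the protocol: N = 100, all MRI-positive at the spine by entry. Assumed: P = 90 participants are PET-positive, so agreement is 90/100; the number truly with TB, D, is varied from 70 to 95. Let a be the number with TB who are PET-positive. Then

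- max(0, P − (N − D)) ≤ a ≤ min(D, P)
- sensitivity = a / D
- specificity = 1 − (P − a) / (N − D)

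| True TB (D) | Without TB | Range of a | Sensitivity | Specificity |
|---|---|---|---|---|
| 95 | 5 | 85 to 90 | 89.5% to 94.7% | 0% to 100% |
| 90 | 10 | 80 to 90 | 88.9% to 100% | 0% to 100% |
| 80 | 20 | 70 to 80 | 87.5% to 100% | 0% to 50% |
| 70 | 30 | 60 to 70 | 85.7% to 100% | 0% to 33.3% |

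Example at D = 80: with a = 80, ten of the 20 without TB are PET-positive, so specificity is 1 − 10/20 = 50%. With a = 70, all 20 are PET-positive and specificity is 0%. The observed agreement is 90/100 in both cases.

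MRI fares no better. With everyone MRI-positive, its sensitivity in this sample is 100% and its specificity 0% by construction, so superiority of PET/CT over MRI at the spine cannot be estimated fairly from these participants.

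**2. What the tissue results could add.**

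Assumed: the share biopsied, the share with TB on tissue, PET/CT sensitivity about 90% and specificity about 80%. Exact (Clopper-Pearson) 95% limits for x of n are the 0.025 quantile of Beta(x, n − x + 1) and the 0.975 quantile of Beta(x + 1, n − x).

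| Biopsied | TB on tissue | Sensitivity (95% CI) | Specificity (95% CI) |
|---|---|---|---|
| 30 | 27 (90%) | 24/27 (70.8% to 97.6%) | 2/3 (9.4% to 99.2%) |
| 50 | 40 (80%) | 36/40 (76.3% to 97.2%) | 8/10 (44.4% to 97.5%) |
| 100 | 80 (80%) | 72/80 (81.2% to 95.6%) | 16/20 (56.3% to 94.3%) |

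Sensitivity becomes estimable. Specificity becomes estimable too, but stays imprecise, because few MRI-selected patients are expected to be negative on tissue.

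**3. Whether an AUC for SUVmax would do better.**

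The Hanley-McNeil variance is [A(1 − A) + (n₁ − 1)(q₁ − A²) + (n₂ − 1)(q₂ − A²)] / (n₁n₂), with q₁ = A/(2 − A) and q₂ = 2A²/(1 + A). At an assumed A = 0.8, q₁ = 0.667 and q₂ = 0.711.

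- 36 confirmed against 4 unconfirmed: variance 1.307/144 = 0.00907, half-width 1.96 × 0.0953 = 0.19.
- 60 against 20: variance 3.084/1200 = 0.00257, half-width 1.96 × 0.0507 = 0.10.

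The formula is asymmetric. With the two groups exchanged, the half-widths are about 0.27 and 0.13. An AUC is feasible but weak.

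**The case against.** The best defence is that the bracketed term is a loose label. The working aim is to evaluate the role of PET/CT in diagnosis; Section 1 calls MRI the standard imaging modality, so MRI is a legitimate imaging comparator. The Rationale also says that "SUVmax will direct to the site for biopsy", which has PET/CT guiding tissue sampling. This stands in part: comparing two images is a reasonable descriptive aim, and the fault is in what the comparison is said to evaluate.

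A reader might infer three stronger things.

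- That agreement carries no information about tissue. The first table shows otherwise: with the TB share known, agreement bounds sensitivity fairly tightly.
- That the tissue results go unused. Section 4.1 uses biopsy or surgery to confirm the clinical diagnosis. What is missing is their use in evaluating PET/CT.
- That the study means to replace biopsy. No section proposes omitting tissue.

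A further objection is that tissue is itself an imperfect reference here. Specimens are taken by clinical indication and after PET/CT. If SUVmax chooses the site, verification depends on the test being evaluated. The exclusion "Suspicion of malignancy on MRI or known malignancy", with that of suspected inflammatory disease, removes many of the alternatives PET/CT would have to tell apart from TB. An unconfirmed specimen is also not proof of no TB. All of this stands, and it limits what the fix can deliver.

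Finally, an unseen analysis plan could name a reference standard. It could, but it would then be adding to an objective that names only MRI.

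**Conclusion.** The point holds as a mismatch between the label and the comparison. PET-MRI agreement at patient level, in a cohort selected on MRI, leaves PET/CT specificity largely unidentified and cannot by itself show that PET/CT can stand in for tissue. At an assumed 90/100 agreement the compatible specificity runs from 0% to 100% with a true TB share of 90% or 95%, and its upper limit falls to 33.3% at 70%. The agreement level and the TB shares are assumptions; MRI positivity at the spine follows from the entry text.

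The argument concerns the spine at patient level. It does not make MRI an improper comparator for describing the distribution of lesions (secondary objective 1). The matter affects one secondary objective and Hypothesis 3. It drives neither the sample size nor the primary objective. It is worth correcting because the correction is cheap and the label invites a conclusion the comparison cannot carry.

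**What to change.** 1. In the synopsis and Section 3, describe the baseline PET/CT-MRI comparison as descriptive concordance and remove the virtual-biopsy label from it.
2. Add an exploratory analysis in participants with a spinal specimen: tabulate first PET/CT findings and SUVmax against MGIT/Xpert confirmation, with the number verified out of those enrolled and exact 95% confidence intervals. An AUC is optional, given the few unconfirmed patients expected.
3. State the limits beside it: tissue taken by clinical indication after PET/CT, possible direction of the biopsy site by SUVmax, exclusion of suspected malignancy and inflammatory disease, and the fact that an unconfirmed specimen does not rule out TB.

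The cost is wording plus one analysis of data already scheduled. No new visit, scan or specimen is needed, and the indications for biopsy or surgery are untouched. The downside is a more modest and imprecise claim in a selected subset.
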